**Assessment Procedures**

Assessments will be conducted at 12M and 24M (critical transition points for both parenting and child development) by highly trained, bilingual research staff, masked to intervention condition, to reduce bias. Assessments will last ~1 hour, in line with prior studies of parents of young children. Assessments will include surveys/questionnaires, observations of parents and children, and direct child assessments.

Outcomes to be assessed via questionnaire include:

|  | | | | | |
| --- | --- | --- | --- | --- | --- |
| **Level** | **Construct** | **Instrument** | **Base-line** | **12M** | **24M** |
| Effectiveness Outcomes | | | | | |
| Parent | **Parent-Child Relationship Quality** | Adult-Child Relationship Scale (*α*=.69-.84)^142^ |  | x | x |
|  | **Responsivity/Cognitive Stimulation** | StimQ Reading, Teaching/Play, Verbal Responsivity (*α*=.88)^143^ |  | x | x |
|  | Stress/Mental Health | Edinburgh Depression Scale (*α*=.77-.86)^144^, Perceived Stress Scale ( *α*=.75-.91);^145^ | x | x | x |
|  | Self-Efficacy | Parenting Self-Agency Measure (*α*=.68-.7)^146^ | x | x | x |
|  | Social Support | General Life Satisfaction (*α*=.91),^147^ Dyadic Adjustment Scale (*α*=.7-.95)^148^ | x | x | x |
|  | Structure | limit-setting, proactive parenting, feeding/sleep/screentime routines,^149^ Socolar Discipline Survey (*α*=.56-.82)^150^ |  | x | x |
|  |  | HealthySteps Parent Feedback Survey^170^ |  | x | x |
|  |  | Parenting Daily Hassles^171^ |  | x | x |
| Child | **Social Competence** | Infant Behavior Questionnaire (*α*=.75-.78),^151^ Brief Infant Toddler Social-Emotional Assessment (*α*=.69-.8)^152^ |  | x |  |
|  |  | Child Behavior Checklist (α=.9-.94)^153^ |  |  | x |
|  | Language & Cognitive Development | Early Social Communication Scale (*α*=.61-.91),^154^  MacArthur-Bates Communicative Development Inventories (*α*=.86);^155^  Dual Language Learners English-Spanish Inventories^172^ |  | x | x |
| Implementation Outcomes (CFIR, RE-AIM, CIHS) | | | | | |
| EBPI Provider (care-team member) | Acceptability | Acceptability of Intervention Measure (AIM; *α*=.89)^158^ |  | x | x |
|  | Appropriateness | Intervention Appropriateness Measure (IAM; *α*=.87)^158^ |  | x | x |
|  | CFIR Domains | Evidence-based Practice Attitudes Scale-36 (*α*=.80),^159^ clinic culture, perceived complexity of intervention, external policies, competence | x | x | x |
|  | Acceptability | Parent satisfaction surveys^117^ |  | x | x |
|  | | | | | |

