In addition, we will assess parent-child relationship quality through observation of videotaped interactions between parents and children at 12 months and 2 years, including play, shared reading, and teaching activities, with global coding of parent and child interaction quality (e.g., responsiveness, sensitivity, positive/negative regard).^138-141^

Direct assessment of child language development using the Receptive and Expressive One-Word Picture Vocabulary Tests^156,157^ will be conducted at the 2 year assessment.

Finally, qualitative interviews will be conducted to examine implementation outcomes, including:

| **Level** | **Domains** | **Measure** | **Base-line** | **12M** | **24M** |
| --- | --- | --- | --- | --- | --- |
| EBPI Provider (care-team member) | Acceptability | ease of program delivery, confidence/efficacy of program delivery |  |  | x |
|  | Appropriateness | perception that program meets needs of patient population |  |  | x |
|  | Fidelity | adherence and perceptions of program delivery |  |  | x |
|  | CFIR Domains | clinic culture, perceived complexity of intervention, external policies, competence |  |  | x |
|  | Acceptability | Parent satisfaction with intervention components |  |  | x |
| Parent | Appropriateness | perceptions that needs are met, content/coverage/frequency/ duration of program sessions, “essential” components |  |  | x |
|  | CFIR Domains | home environment, family needs, resources, motivation |  |  | x |
|  | CFIR Domains | home environment, family needs, resources, motivation |  |  | x |

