# Statistical Considerations

## Statistical and Analytical Plans

***Effectiveness Outcomes***

Initial ANOVA and Chi-square tests will be conducted to examine baseline equivalence of randomly assigned groups. Analyses with sex as a biological variable, including moderation and subgroup analyses, will be performed. Covariate entry (e.g., sociodemographics) will be decided based on model fit criteria, and sensitivity analyses will be performed for post-randomization risks.

Missing data and attrition: The research team has expertise in minimizing missing data. In addition, multiple imputation (MI)^160^ will be used to replace item-level data using the rich array of concurrently collected variables and prior responses. If an entire measure/survey is missing, we will use chained equations with lagged (in time) variables^161^ using all available information to build a large set of imputed datasets. Estimates will be combined using Rubin’s rules.^160^ When data are Missing at Random, likelihood-based methods provide unbiased estimates of population parameters even when panels are incomplete. In addition, we will use attrition analyses^162^ to examine whether attrition is related to baseline characteristics.

Tests of hypotheses: In order to examine the added value of HS+VIP in comparison to the standard HS model, we will focus on outcomes related to ERH and ECD where we expect the effects of standard HS to be substantially smaller than the integrated HS+VIP model. Impact analyses at each assessment timepoint will be conducted using ordinary least squares (OLS) regression in an intent-to-treat (ITT) framework, adjusted for baseline sociodemographic covariates. In addition, structural equation models (SEM)^163^ will be used to examine family outcomes over time. This will allow us to examine whether initial levels and trajectories in parent well-being, parent-child interaction, and ECD vary between participants, and whether that variation is explained by assignment to HS+VIP or standard HS.

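### Growth models of individual trajectories are planned for parent-child interaction and child development, but the measures table gives these outcomes at most two waves, both after randomisation

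*Protocol*

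**What the plan says.** Section 9.1 (Effectiveness Outcomes) first plans OLS regression by intention to treat at each assessment. It then adds that "structural equation models (SEM)^163^ will be used to examine family outcomes over time". The stated purpose is to learn "whether initial levels and trajectories in parent well-being, parent-child interaction, and ECD vary between participants", and whether assignment explains that variation. No growth form, residual constraint or set of indicators is given.

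Section 7.1.1 sets the schedule by instrument. The relationship scale's row reads "Adult-Child Relationship Scale (*α*=.69-.84)^142^ | | x | x", with the baseline cell empty. StimQ and the parent-report and communication measures of language follow the same pattern. For observation, "we will assess parent-child relationship quality through observation of videotaped interactions between parents and children at 12 months and 2 years". Social competence uses the Infant Behavior Questionnaire and the "Brief Infant Toddler Social-Emotional Assessment" at 12M, then the "Child Behavior Checklist" at 24M. The direct vocabulary tests are given at 2 years only. Depression, stress, self-efficacy and social support are measured at baseline, 12M and 24M. Randomisation follows baseline.

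Other places differ. The Protocol Summary (Key Procedures) lists child assessments and observations under enrollment, 12m and 24m. Sections 4.1 and 7.1 place outcomes including the parent-child relationship and child development at baseline, 12 months and 2 years. The baseline visit in section 7.3.2 collects information on children's development without naming an instrument.

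**The concern.** Section 9.1 asks one longitudinal question of three groups of outcomes that do not have the same data behind them. Whether families differ in trajectory is a question about slope variance. Two scores per family cannot separate true differences in slope from measurement error unless something further is assumed or added.

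The coefficients also change meaning between outcomes. For parent well-being, the initial level precedes randomisation and benefit shows in the slope. For relationship and child development outcomes the first wave is 12M, by which time section 9.4.4 (Planned Interim Analysis) counts 6–12 months of intervention. An arm difference in that level is itself a treatment effect. A benefit already present at 12M and held to 24M gives a level difference and a zero slope difference, and a reader of the trajectory result alone could take that as no effect. These are the outcomes on which section 9.1 says the comparison will focus.

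**Working it through.** **The plan's own figure.** Section 9.5 expects 400 families at the end: 500 × (1 − 0.20) = 400, or 200 per arm. With d = 0.30 and alpha .05 (two-sided assumed), 0.30 × √(200/2) = 3.00, and power = Φ(3.00 − 1.96) = 85.1% (84.9% by the t test). The stated figure of more than 80% reproduces. The present point does not depend on it.

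**Waves by instrument (section 7.1.1).**

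| Outcome | Instrument | Baseline | 12M | 24M |
|---|---|---|---|---|
| Relationship quality | Adult-Child Relationship Scale | – | x | x |
| Cognitive stimulation | StimQ | – | x | x |
| Observed interaction | Coded video | – | x | x |
| Language | Early Social Communication Scale, MacArthur-Bates, dual-language inventories | – | x | x |
| Social competence | Infant Behavior Questionnaire, Brief Infant Toddler assessment | – | x | – |
| Social competence | Child Behavior Checklist | – | – | x |
| Direct vocabulary | One-word picture tests | – | – | x |
| Parent stress, mental health, self-efficacy, support | Several scales | x | x | x |

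**Which schedule is operative.** Three other places agree with the table. The schematic shows relationship and child development outcomes only at 12m and 24m. The visit lists in section 7.3 name parent-child observation at Visits 2 and 3 but not at baseline. Section 14.3 pays up to $145, which is 3 × $25 + 2 × $35: three surveys and two in-person assessments.

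**Parameter count.** Take a linear growth model with one score per wave and arm predicting level and slope.

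- Two waves supply 2 means + 2 arm effects + 2 variances + 1 covariance = 7 moments.
- The model needs 2 growth means + 2 arm effects + level variance, slope variance and their covariance = 7 parameters, plus residual variances.
- Equal residuals: 8 parameters, df = 7 − 8 = −1. Free residuals: 9 parameters, df = −2. The numerical rank is 7 in both, so neither is identified.
- Residual variance fixed at zero: 7 parameters, df = 0, just identified. This is a change-score model.
- Three waves supply 3 + 3 + 6 = 12 moments: df = 12 − 8 = 4 with equal residuals, 12 − 10 = 2 with free residuals. Both are identified.

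**What is lost.** Let V1 and V2 be the variances at 12M and 24M, C the covariance and θ a common residual variance. Then:

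- level variance = V1 − θ
- level-slope covariance = C − V1 + θ
- slope variance = V1 + V2 − 2C − 2θ

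Every admissible θ reproduces the same data, so these three quantities are undetermined. The growth means and both arm effects do not involve θ and remain estimable.

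**How much θ matters (illustration).** Set V1 = V2 = 1, take the relationship scale's alphas (.69–.84) as reliability, so θ = .31 to .16, and assume a 12M–24M correlation r, which the protocol does not give. The share of change variance that is true change is (ρ − r)/(1 − r):

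| Assumed r | ρ = .69 | ρ = .84 |
|---|---|---|
| .3 | .56 | .77 |
| .5 | .38 | .68 |
| .6 | .23 | .60 |

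For StimQ (alpha .88) at r = .5 it is (.88 − .5)/.5 = .76. Fixing θ at zero sets every entry to 1 by assumption.

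**Reading the slope.** If the arm difference is 0.30 SD at both 12M and 24M, the level effect is 0.30 and the slope effect is 0.30 − 0.30 = 0.

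**The case against.** The strongest reply is that the protocol does not commit to the model counted above. Section 9.1 says only SEM, and section 9.5 refers to item reliability, which suggests latent variables with several indicators. For instruments repeated at both visits, a multi-indicator latent-change model with measurement invariance can separate error from change, and its details could properly sit in a SAP. This stands, and it limits the identification point to the ordinary single-score growth model. It does not supply a third wave, nor a same-instrument trajectory for social competence or direct vocabulary, although section 9.1 does not say that trajectories will be fitted to those measures in particular.

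A reader might also infer that no longitudinal treatment effect is estimable, or that the trial's main comparison is damaged. The document supports neither. Mean arm effects on 12M level and 12M–24M change are identified with two waves. The OLS analyses at each timepoint would show a sustained benefit at both visits, which largely protects against misreading a null slope. Low reliability of change costs precision but does not bias a randomised difference in change.

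Finally, it cannot be taken as settled that nothing is measured at baseline: the Protocol Summary and sections 4.1, 7.1 and 7.3.2 point the other way. Baselines on the same instruments would give three waves. The instrument-level text is the more specific, but the conflict needs resolving.

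**Conclusion.** The concern holds in limited form. Under the section 7.1.1 schedule, an ordinary single-score growth model cannot estimate how families vary in level and trajectory for parent-child interaction, relationship or child development outcomes: it is short by one or two degrees of freedom. The first wave of these outcomes is post-treatment, so their initial level must be read as a treatment effect under any specification. For social competence and direct vocabulary no same-instrument trajectory exists.

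The conclusion assumes that the measures table and its accompanying text are the operative schedule and that each wave contributes one score. The reliability figures are illustrative and rest on an assumed correlation. Parent well-being and the visit-by-visit intent-to-treat analyses are sound on this point. What is at stake is a supplementary longitudinal claim, but one the protocol states explicitly, and it should be corrected before analysis.

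**What to change.** 1. Reconcile the Protocol Summary and sections 4.1, 7.1 and 7.3.2 with section 7.1.1 on what is measured at baseline, and with which instrument.
2. In section 9.1, restrict growth-curve SEM to measures taken at baseline, 12M and 24M.
3. For relationship and child development instruments repeated at 12M and 24M, specify a two-visit intent-to-treat model with arm, visit and their interaction, or a multi-indicator latent-change model with measurement invariance. State that the 12M level is a treatment outcome, and report arm differences at both visits.
4. Make no trajectory claim for social competence or direct vocabulary. They keep the single-visit intent-to-treat regression already planned.

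The cost is a change of wording with no new data. The individual-trajectory claim is given up for two-wave outcomes.

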### Study Specific Procedures

**Randomization Procedures**

We will use simple randomization with a maximum tolerated imbalance procedure. Before randomization to HS+PlayReadVIP or standard HS, enrolled families will complete baseline assessments. Families will receive HS+PlayReadVIP or standard HS at each well-child visit through 24M.

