## Measures to Minimize Bias

### Enrollment/Randomization/Masking Procedures

***Enrollment Procedures:***

Consecutive enrollment of eligible participants, based on screening of inclusion/exclusion criteria by study staff, will take place at the SPFHC pediatric clinic. Baseline assessments, including demographic data and initial surveys/questionnaires, will be conducted at the time of enrollment, after informed consent is collected but before randomization.

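### The growth SEM asks whether assignment explains the starting level of five parent well-being scales that are measured before randomisation; fixing that path at zero recovers precision

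*Protocol*

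**What the plan says.** Section 9.1 (Effectiveness Outcomes, tests of hypotheses) makes OLS the impact analysis: "Impact analyses at each assessment timepoint will be conducted using ordinary least squares (OLS) regression in an intent-to-treat (ITT) framework, adjusted for baseline sociodemographic covariates". A second model is then added: "In addition, structural equation models (SEM)^163^ will be used to examine family outcomes over time". Its stated question is "whether initial levels and trajectories in parent well-being, parent-child interaction, and ECD vary between participants, and whether that variation is explained by assignment" to one of the two programmes.

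The order of baseline and randomisation is stated twice. Section 7.1.1 (Randomization Procedures) says "Before randomization to HS+PlayReadVIP or standard HS, enrolled families will complete baseline assessments", and section 9.6.1 puts baseline assessments "after informed consent is collected but before randomization".

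The instrument table in section 7.1.1 (Assessment Procedures) shows which outcomes have a baseline score. Stress and mental health are marked at all three waves, for example "Perceived Stress Scale ( *α*=.75-.91);^145^ | x | x | x", and self-efficacy and social support carry the same three marks. That makes five scales: Edinburgh Depression, Perceived Stress, Parenting Self-Agency, General Life Satisfaction and Dyadic Adjustment. Relationship quality starts at 12M: "Adult-Child Relationship Scale (*α*=.69-.84)^142^ | | x | x". StimQ, structure and discipline, and every child instrument also have no baseline mark, and observed interaction is scheduled only at 12 months and 2 years. Section 7.3.2 mentions baseline information on children's development, but no child instrument is marked there.

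**The concern.** The quoted question treats three domains alike, but their first measurements fall on opposite sides of randomisation. For the five parent well-being scales the initial level precedes assignment, so the true arm effect on it is zero by design. Asking whether assignment explains it has two consequences.

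First, a chance baseline difference can be reported as variation explained by the programme. Second, if the model estimates an arm effect on the intercept, the arm effect on the slope becomes in essence a comparison of change scores. It no longer uses the fact that both arms start from the same mean, and its standard error is larger than the same data require.

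Parent mental health is listed among the primary endpoints in section 4.2.1, so the longitudinal test of these scales is of some consequence.

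**Working it through.** **Inputs from the protocol.** Final sample 400 of 500 enrolled, d = .30, alpha = .05 (section 9.5). Two arms with a maximum imbalance of 4, so about 200 per arm (section 9.6.1). Visits at Day 0, 180 and 540, so months 0, 6 and 18 (sections 7.3.2 to 7.3.4).

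**Assumptions.** Two-sided test, complete data, unit variance, linear growth, the same correlation rho between any two waves, and an effect that reaches .30 at the last visit. The protocol gives no rho, so I show .3 to .7.

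**The plan's own figure.** 500 × 0.80 = 400. The standard error of a difference in means is √(2/200) = 0.100, and power is Φ(.30/.100 − 1.96) = .851. This agrees with the claim of more than 80% in section 9.5.

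**Path free.** The visit times have mean 8 and sum of squared deviations 64 + 4 + 100 = 168. The arm effect on change to month 18 has variance

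V(free) = (2/200) × (1 − rho) × 18²/168 = 0.01 × (1 − rho) × 1.929.

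**Path fixed at zero.** The variance falls by the squared correlation between the estimated arm effects on intercept and slope:

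cut = 64(1 − rho) / [120(1 − rho) + 168 rho] = 8(1 − rho) / (15 + 6 rho).

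At rho = .5: V(free) = 0.00964, SE .0982, power Φ(.30/.0982 − 1.96) = .86. The cut is 4/18 = 22.2%, so V(fixed) = 0.00750, SE .0866, power Φ(.30/.0866 − 1.96) = .93.

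| rho | SE, path free | SE, path fixed | variance cut | power, free | power, fixed |
|---|---|---|---|---|---|
| .3 | .1162 | .0949 | 33.3% | .73 | .89 |
| .4 | .1076 | .0915 | 27.6% | .80 | .91 |
| .5 | .0982 | .0866 | 22.2% | .86 | .93 |
| .6 | .0878 | .0799 | 17.2% | .93 | .96 |
| .7 | .0761 | .0712 | 12.5% | .98 | .99 |

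A direct generalised least squares calculation gives the same standard errors.

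**Cross-check with two waves.** Change score against baseline-constrained comparison: the variance ratio is (1 − rho²) / [2(1 − rho)] = (1 + rho)/2. That is .65 at rho = .3 and .75 at .5, which are cuts of 35% and 25%. The order of size is the same.

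**Sensitivity.** At rho = .3 and .4 the free-path slope test (.73, .80) has less power than a 24M comparison that ignores baseline altogether (.85). If the model-implied difference at 24M is tested instead of the slope, the free path inflates the standard error by 3% at rho = .3, 13% at .5 and 39% at .7.

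**Chance baseline effects.** Each test has a 5% chance of a false signal. Over five scales, 1 − .95⁵ = 22.6% for at least one. This is an upper guide: it assumes independent, uncorrected tests, whereas the scales are probably correlated and section 9.4.6 names a false discovery rate procedure.

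**The case against.** The strongest reply has four parts.

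- **The model is inferred.** Section 9.1 gives no path diagram, time coding or constraints, and an SAP may settle these. That is fair as to how the model will be fitted. It does not rescue the question, which the protocol states itself and which has no meaningful answer for the five scales.
- **The analysis is supplementary.** OLS carries the impact analysis, and the hypothesis section says "we will focus on outcomes related to ERH and ECD", not parent well-being. This stands and limits the importance of the point.
- **Nothing is biased.** Under randomisation the free path leaves the slope effect unbiased. This stands; the cost is precision only.
- **The gain depends on rho.** This stands too. Free-path power is already about .80 or higher from rho = .4 upward, and at .7 the gain is only .98 to .99.

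A reader might also infer that initial levels should be removed from the question altogether. The documents do not support that. Parent-child interaction and child development are first measured at 12M, about six months after enrolment by the visit schedule, so an arm difference in that first level is a real treatment effect.

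Nor can the free path be blamed for any disagreement between SEM and OLS. The OLS model is described as adjusting for sociodemographic covariates and names no baseline outcome score. It may therefore carry chance baseline imbalance itself, and could differ from a constrained model as well.

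**Conclusion.** The point holds for the five parent well-being scales with a pre-randomisation score, and for no other outcome. For these, the arm effect on the initial level is zero by design, and estimating it costs precision. Under the assumptions above, fixing the path cuts the variance of the slope effect by 12.5% to 33% over rho = .7 to .3. Another correlation structure or other visit times would change these figures.

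A reader might take this as a fault in the main effectiveness analysis or in the sample size. It is neither: the per-timepoint OLS analyses and the power in section 9.5 are untouched. It is a modest but nearly free improvement to a supplementary analysis, and it removes a question that the design cannot answer.

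**What to change.** Revise the SEM sentence in section 9.1 so that it separates the two kinds of outcome:

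- For outcomes with a pre-randomisation score, constrain the arms to a common baseline mean (arm effect on the initial level fixed at zero) and test assignment only on change to 12M and 24M.
- For outcomes first measured at 12M (parent-child relationship and interaction, StimQ, structure, child development), keep the 12M level as a post-randomisation treatment effect, with no constraint.

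The cost is one sentence and one model constraint. No new data are needed, and randomisation justifies the constraint.
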